### Data Management

A management committee (MA, SA, and LAS) is formed to monitor data quality and to approve any decision in the present trial. Data entry and coding will be conducted by people other than the main research team and will be checked by the management committee through range-checks for data values.

### Statistical Analysis

The normal quantitative variables (checked via the Kolmogorov–Smirnov normality test) will be described using mean and standard deviation. The rest of data will be described using median and interquartile range. To compare the two research groups in terms of the mean difference of quantitative variables, if the normality assumption is met, an independent-sample *T*-test will be run. Otherwise, Mann–Whitney *U*-test will be employed. To test the homogeneity of qualitative variables in the two groups, the Chi-squared test and Fisher's exact test will be run at the *p*-value of 0.05. Repeated-measures or equivalent non-parametric tests will be employed for the continuous outcomes measured repeatedly. All these tests will be two-tailed at a 5 % significance level. Statistical analyses will be done in SPSS22. The analysis will be conducted on an intention to treat. No interim analyses are planned.

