### Outcome Measures

#### Primary Outcomes

The primary outcome will be a change to the patient's depression anxiety stress scales-21 (DASS-21) score from baseline to 2 weeks after discharge from hospital. It will be measured at the baseline, upon discharge and 2 weeks afterward. It should be noted that baseline measurements will be collected as soon as the patient is admitted to the hospital. This will ensure that almost all patients are included under the same conditions.

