### Sample Size

The similar research was used to estimate the sample size. The most similar study to the present work was conducted by Proudfoot et al. (31), who explored the effect of a mobile application on stress, anxiety and depression. In the above-mentioned research, after the intervention, the effect size between the control and intervention group (the one provided with the application) was reported to be 0.41. The sample size is estimated 190 in total (95 for the intervention group and 95 for the control group) which is calculated in G^*^Power software with an effect size of 0.41, error probability of 0.05, power of 0.8, and allocation ratio of 1:1. Regarding the 10 % attrition rate within the study, the goal is to include 105 patients in each group (210 participants overall).

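### The primary DASS-21 analysis is not fixed: several tests are named, a normality pre-test chooses between two of them, and none adjusts for baseline DASS-21

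*Protocol article*

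**What the plan says.** All references are to the protocol article.

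- **Primary Outcomes** defines the outcome as change in DASS-21 from baseline to two weeks after discharge, and says of the score: "It will be measured at the baseline, upon discharge and 2 weeks afterward".
- **Statistical Analysis** gives the two-group comparison: "To compare the two research groups in terms of the mean difference of quantitative variables, if the normality assumption is met, an independent-sample" t-test is used; if not, a Mann-Whitney test. Normality is judged by Kolmogorov-Smirnov. The same section then assigns repeated-measures methods, or non-parametric counterparts, to continuous outcomes that are measured repeatedly. DASS-21, with three measurements, is such an outcome. The section does not say which of these analyses carries the primary conclusion, and it names no baseline covariate.
- **Randomization** has the envelopes opened only after consent and the baseline assessments, so baseline DASS-21 precedes knowledge of the allocation.
- **Sample Size** takes its effect size from a similar study, in which "after the intervention, the effect size between the control and intervention group (the one provided with the application) was reported to be 0.41". It does not say which SD that figure is scaled on.
- **Data Collection Instruments** describes three subscales, each scored 0 to 21, as the main indicators.

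**The concern.** There are two separate problems.

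**The analysis is left open.** A t-test estimates a difference in means. Mann-Whitney compares ranks and gives no mean change. If a pre-test on the trial's own data chooses between them, the quantity reported is known only once the data are in. The rank branch could well be taken, because the subscales are bounded integer scores. The repeated-measures sentence adds a further choice for the same outcome, with its own parametric or non-parametric branch. If these analyses disagree, the plan does not say which one decides.

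**Baseline is not used as a covariate.** Baseline DASS-21 is a valid covariate that is already being collected. An unadjusted change score subtracts the whole of any chance baseline imbalance, while with equal SDs only a fraction r of it is expected to carry through to follow-up. The comparison stays valid under randomisation but gives up precision that costs nothing to keep.

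**Working it through.** **Inputs.** Sample Size gives the calculation "with an effect size of 0.41, error probability of 0.05, power of 0.8, and allocation ratio of 1:1". Statistical Analysis adds "All these tests will be two-tailed". The result is stated as "The sample size is estimated 190 in total (95 for the intervention group and 95 for the control group". (The abstract gives a different total, 112. That is a separate matter; 95 per arm is used here.)

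**Step 1: reproduce the plan's figure.** By normal approximation, n per arm = 2(1.960 + 0.842)² / 0.41² = 93.4, so 94. The exact two-sided t-test gives 94.35, so 95, with power 80.3% at 95 per arm. The stated figure reproduces. A one-sided test would need only about 75.

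**Step 2: precision.** Let σ be the DASS-21 SD, assumed equal at baseline and follow-up, and r the correlation between baseline and the two-week score. The document does not give r, so it is varied.

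- Variance of change: 2σ²(1 − r)
- Residual variance under ANCOVA: σ²(1 − r²)
- Ratio, ANCOVA to change: (1 + r)/2, which is 0.65 at r = 0.3, 0.75 at r = 0.5 and 0.85 at r = 0.7

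The ratio is below 1 for every r below 1.

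**Step 3: power at 95 per arm if 0.41 is scaled on the follow-up SD.** Then d for change = 0.41/√(2(1 − r)) and d for ANCOVA = 0.41/√(1 − r²). At r = 0.3 these are 0.41/√1.4 = 0.347 and 0.41/√0.91 = 0.430.

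| r | d, change | Power, change | n per arm for 80% | d, ANCOVA | Power, ANCOVA | n per arm for 80% |
|---|---|---|---|---|---|---|
| 0.3 | 0.347 | 66% | 132 | 0.430 | 84% | 86 |
| 0.4 | 0.374 | 73% | 114 | 0.447 | 87% | 80 |
| 0.5 | 0.410 | 80% | 95 | 0.473 | 90% | 72 |
| 0.6 | 0.458 | 88% | 76 | 0.512 | 94% | 61 |
| 0.7 | 0.529 | 95% | 58 | 0.574 | 98% | 49 |

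The change test drops below 80% only when r is below 0.5.

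**Step 4: power at 95 per arm if 0.41 is scaled on the SD of change.** The change test keeps 80.3% at any r. For ANCOVA, d = 0.41√(2/(1 + r)), which is 0.509, 0.473 and 0.445 at r = 0.3, 0.5 and 0.7. Power is 94%, 90% and 86%.

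**Step 5: does the repeated-measures route supply the adjustment?** Plain repeated-measures ANOVA treats baseline as one of the outcomes, not as a covariate. With two time points its group-by-time test is the change-score t-test. With three time points, assume the same correlation r between any two occasions and a difference of 0.41 follow-up SDs at both discharge and two weeks. The group-by-time test then has power 69%, 84% and 97% at r = 0.3, 0.5 and 0.7, and the group main effect 73%, 63% and 55%. The choice of test within this route therefore matters, and the section does not make it.

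**Step 6: cost of the rank test.** If the data are normal, Mann-Whitney has asymptotic relative efficiency 0.955, so it needs 94.35/0.955 = 98.8, about 99 per arm against 95. The power loss is small. The objection to this branch is the change in what is estimated.

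**The case against.** - **A change-score comparison is valid and unbiased in a randomised trial.** This stands. ANCOVA is a gain in efficiency and does not correct an error.
- **Model covariates are commonly left to a full protocol or SAP, and neither is shown.** This stands in part: a missing covariate alone would be weak ground. But the article does set out an analysis rule, and that rule has a data-driven branch and competing tests for one primary outcome.
- **The t-test or Mann-Whitney test on raw change is not shown to be the primary analysis.** This stands. A reader might infer that it is, by joining the outcome definition to the two-group test. But a mean difference can also mean a difference between group means, and the repeated-measures sentence covers DASS-21 as well. What the text supports is that no analysis is fixed as primary.
- **The trial is not shown to miss its 80% power.** This stands too. A reader might infer a shortfall from the lower rows of r in the table, but that needs both r below 0.5 and an effect size scaled on the follow-up SD. The document gives neither. Its only stability figures, intra-class correlations of 0.77 to 0.89, are retest reliabilities. They do not settle the correlation from admission through recovery, and they lend no support to a low value. If r were that high, the change test would exceed 80%.

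**Conclusion.** The point holds as one of specification and efficiency. The plan names competing analyses of the primary outcome, lets a Kolmogorov-Smirnov test choose between a mean and a rank comparison, designates none as primary, and adjusts for baseline DASS-21 in none of them. This much rests on the text alone.

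The efficiency gain rests on equal SDs at the two times and a linear relation to baseline. ANCOVA then needs 65% to 85% of the variance of unadjusted change for r from 0.3 to 0.7. It has the higher power under either scaling of the 0.41: 84% to 98% against 66% to 95% on the follow-up SD, and 94% to 86% against a constant 80% on the SD of change. A shortfall below the planned power is possible but conditional, and should not be reported as a demonstrated defect.

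**What to change.** In Statistical Analysis, name one primary analysis: ANCOVA of the DASS-21 score at two weeks after discharge on group and baseline DASS-21. An equally good choice is a mixed model of the discharge and two-week scores with baseline as covariate and the two-week group contrast as primary. Apply it in the same way to whichever DASS-21 score or subscales are declared primary.

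Report the adjusted mean difference with its 95% CI whatever the normality test shows, with robust or bootstrap standard errors if the scores are skewed. Remove the Kolmogorov-Smirnov test as a gate for the primary analysis. Keep Mann-Whitney and the repeated-measures tests, labelled as sensitivity or secondary analyses. In Sample Size, state which SD the 0.41 is scaled on.

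The cost is a few sentences. No new data or larger sample is needed, and ANCOVA is available in the planned software.

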## Results

So far, the design procedure has been fulfilled. The recruitment of participants has not been completed and is scheduled not later than March 2021.

## Discussion

The present research, a randomized clinical trial in type, aims to evaluate a mobile application designed to monitor COVID-19 patients and provide them with clinical and psychological feedback compared to usual care. It seems that such an intervention can provide proper support for the peak time of the disease occurrence. The prospective findings will provide evidence for the effect of mobile health on COVID-19 patients. This research, which will be conducted by an interdisciplinary team, makes it possible to evaluate the effect of this intervention precisely.

Mobile-based interventions can be effective in all stages of prevention, treatment, and follow-up. Instances are checking symptoms, educating patients, communicating with patients and adhering to treatment. Different studies have dealt with the effect of mobile applications on stress and anxiety management and managed to control them (14–16). Thus, it seems that providing psychological support for COVID-19 patients can reduce mental pressure, signs of depression and anxiety (32).

Providing mental healthcare services is not only essential for patients with COVID-19 but also for all individuals who are at a higher risk of the disease. Preliminary reports show that, during the pandemic, people are actively searching for online services to meet their mental health needs. It proves public interest in and acceptance of the medium (33). China, as the first country faced with the coronavirus, has been actively involved in providing different telemental health services during the pandemic. These services have been provided by academic and governmental organizations and include online counseling, supervision, training, and psychoeducation. Research findings proved the effectiveness of online telemental health services and social networks in improving patients' tolerance and stress (34).

Among the benefits of telehealth services are enabling individuals to welcome treatments, cooperate in diagnostic and therapeutic measures, and giving them personal feedback, and supporting or motivating them (35).

The three factors of physician, patient and disease play a key role in the therapeutic process of a disease. If the first two are united, they can pass through the third (i.e., the disease). To unite the physician and patient, it is essential to create connections and interactions between them, possibly facilitated by mobile-assisted technologies (36). We set this issue as a main goal in SarveDigital development. Thus, the instrument developed will enable patients to report their clinical and psychological problems to the medical staff at almost any time. Moreover, this two-way communication will help patients to be actively involved in the treatment procedure, as advised by the physician. There is no harm in using a mobile phone by COVID-19 patients and this is a right preserved for them.

The majority of patients are only examined once a day by the attending physician. Therefore, reporting the respiratory, physical, and mental conditions to the attending physician can create a sense of trust in the medical system and can reduce anxiety. It is in line with the results of a study by Noee et al. (37) which investigated the potential applications of mobile apps in the Iranian health system based on physician opinions. In the light of the present findings, to further develop mobile-assisted healthcare services in Iran, the priorities are: recording and tracking vital signs, supporting electronic decision-making in health-related issues, providing healthcare for remote areas, improving service quality, selecting the best health behavioral patterns, raising social awareness and improving health-related behavior, and increasing patients' knowledge of the disease (37).

It seems that, within the complications of COVID-19 pandemic, most of the above-mentioned priorities should be considered in the applications designed so that we can hope to manage the disease.

An investigation of the existing healthcare applications in Iran shows that the design and development of mobile health applications have grown at least quantitatively in recent years. Considering the fact that Iran is among the top-ranking Middle-eastern countries using mobile phones, it is not far from expectation to warmly embrace the health-related applications (36). A review of published literature on mobile health in Iran proves that the mobile health-related body of research is ever increasing in Iran (38). Although Iranian researchers joined this line of research later, the effectiveness of the interventions in this field in Iran further attests to the potential value of the interventions in disease management. COVID-19 pandemic drew further attention to the significance of using telemedicine tools. During the COVID-19 pandemic, Iranian people have been as psychologically pressed as all around the globe (39). More cases of mental health problems have been reported among COVID-19 patients than others (20) which shows the need for systematic and goal-oriented interventions for COVID-19 patients to support them both psychologically and physically.

If SarveDigital proves effective in telemonitoring COVID-19 patients, we can hope such instruments can reduce the medical staff's work pressure, especially those in the front line of battling the disease. It can also help to reduce COVID-19 patients' anxiety and stress.

## Strengths and Limitations of this Study

The self-care mobile application in the present research was designed in a structured way with the help of a multi-disciplinary team.The application addresses specific, well-defined characteristics, including care-providers' education, contact, self-reported symptoms and care-providers' biography. These all can increase the chances of success.The design of this study (randomized controlled trial) tends to meet the highest level of evidence.We cannot blind patients to the nature of the intervention, and this is an alleged limitation in the present research.Some limitations of the present research are the low literacy of using mobile health in the target population and some patients' unwillingness to continue using the application.

## Ethics and Dissemination

The approval was obtained from the Ethics committee of Mashhad University of Medical Sciences on 2020-04-19 (# IR.MUMS.REC.1399.118). This trial was registered in Iran Trial Registrar under IRCT20170922036314N4 registration number and 22 June 2020 registration date. The results will be disseminated in a peer-reviewed journal.

The dataset supporting the present results can be made available by the corresponding author upon reasonable request. Personal information about the potential and enrolled participants will be saved on a secure file server research drive at MUMS to ensure confidentiality before, during and after the research.

## Data Availability Statement

The original contributions presented in the study are included in the article/supplementary material, further inquiries can be directed to the corresponding author/s.

## Ethics Statement

This study was approved by the Ethics Committee of Mashhad University of Medical Sciences and Medical School (Ethical code: IR.MUMS.REC.1399.118).
